### **Summary of the Study**

Multiple Sclerosis (MS) is characterised by significant symptom diversity and complexity. The unpredictability of the symptoms and the emotional and cognitive facets of the disease have a significant impact on the patients' quality of life, relationships and other significant areas of living. Psychological interventions and their efficacy have been the focus of MS literature over the past years and have been found to have moderate effects on quality of life, depression and stress reduction, improvement of wellbeing, anxiety, fatigue and sleep disturbances and emotion regulation. The present research project follows from an exploratory mixed method study on the effects of various forms of psychosocial interventions on the experience and management of MS ([name] et al., 2021). The results of that study generated themes that led to the development of a novel, patient – led psychological intervention named MyMS-Ally. Most interventions so far are based on generic models of therapy which cannot cover the complexity and unpredictability of MS. It is aspired that this patient-led model of intervention will meet the needs and preferences of people with MS. The current study aims to explore the feasibility and acceptability of MyMS-Ally intervention and also obtain preliminary data on the effects on quality of life, emotion regulation, depression and anxiety through the application of a mixed methods design. People with MS will be recruited at the Bristol and Avon Multiple Sclerosis centre. They will participate in MyMS-Ally group intervention for 8 weeks. They will complete quantitative measures before and at the end of the intervention as well as at one and three – months follow – up. Individual semi – structured qualitative interviews will also be conducted before and at the end of the intervention and at 3 – months follow-up. The aim is to explore the relevance, sustainability and adherence to the intervention and study processes (feasibility) as well as the appropriateness of the intervention based on the emotional and cognitive responses, satisfaction and perceived effectiveness (acceptability). The secondary aim of the study is to obtain preliminary data on change processes and outcomes. The study is funded by the Vice – Chancellor's Early Career Researcher Award, University of the West of England.

## **Summary of Main Issues**

### ***Purpose and design***

There are approximately 106.000 Multiple Sclerosis (MS) cases recorded in the United Kingdom (Public Health England, 2020). Living with MS places the person in precarious positioning where continuous behavioural and cognitive modifications are required in confronting physical and psychosocial challenges. People with Multiple Sclerosis face the challenge of integrating the disease into their identity (Dennison, Yardley, Devereux, & Moss-Morris, 2013; Irvine, Davidson, Hoy, & Lowe-Strong, 2009) as they strive to develop a sense of coherence and control over their illness. These processes are positively related to emotional, psychological, and social wellbeing (Bassi et al., 2019; Calandri, Graziano, Borghi & Bonino, 2018). Adjustment to the illness has been associated with positive affect, optimism, self – efficacy and meaning making processes (Calandri et al., 2018). The role of psychotherapy in these processes requires further investigation (Calandri et al., 2018) through systematic exploratory analysis of diverse perspectives (Methley, Chew-Graham, Campbell & Cheraghi-Sohi, 2015).

The literature on psychological interventions has mainly focused on theory-driven models of intervention with Cognitive Behavioural Therapy (CBT) and Mindfulness being the most prominent ones. They have been associated with improvement of wellbeing (Simpson, Simpson, Ramparsad, Lawrence, Booth & Mercer, 2019; Spinzer & Pakenham, 2018), reduction of stress, anxiety, depression, fatigue and sleep disturbances (De la Torre, Mato, Doval, Espinosa et al., 2020; Hind, Cotter, Thake, Bradburn et al., 2014; Miller, Altaras, Vissicchio, Zemon, Portnoy et al., 2020; Pagnini, Cavallera, Rovaris, Mendozzi et al., 2019; Reynard, Burleson – Sullivan & Rae – Gant, 2014). More integrative approaches such as Acceptance and Commitment Therapy and supportive therapy and counselling have been found to contribute to improvements in quality of life, adjustment and coping with MS (Han, 2021; Pakenham, Mawdsley, Brown & Burton, 2018; Molton, Koelmel, Curran, Von Geldern, Ordway & Alschuler, 2019; Topcu et al., 2020).

The recent literature focuses mainly on generic models of psychological interventions which cannot cover the complexity and the unpredictability of MS. However, given recent developments of process – based psychological interventions, psychological approaches can be formulated based upon the specific characteristics of the disease for people with MS. The people with MS' voices and preferences can guide psychological intervention programmes development as well as methods of evaluation of these programmes. The current research

project aims to address the above issues, following from a longitudinal, exploratory, mixed method study on the experience of psychosocial interventions for 20 people with MS ([name], Anagnostopoulos & Triliva, 2021). Results of this study revealed the interplay between MS and psychosocial interventions and the journey of the participants from the despair at diagnosis, helplessness and punishment to the new preferred identity that encompasses the MS body, empowerment and forgiveness. The themes of the study guided the development of the novel group psychological intervention MyMS-Ally and the current research project explores the feasibility and acceptability of this intervention programme.

The primary objective of the current study is the investigation of the feasibility and acceptability of the novel group psychological intervention MyMS-Ally. As a secondary objective, the researchers will collect primary data to evaluate the effects of the intervention on quality of life, depression, anxiety and emotion regulation. A mixed method design will be implemented. Qualitative individual interviews will provide insight into the participants' experiences taking part in the intervention, how they perceive the impact on their experience and management of MS and which intervention processes they perceived as helpful or unhelpful. Quantitative outcome measures will record any potential change. The aim of the study is to reach conclusions with regards to the relevance and appraisals of participants taking part in the intervention so that final modifications are made and the intervention can be further evaluated. Additionally, the study aims to reach statistically significant results that will indicate the impact of the intervention but also to indicate effects that are meaningful in everyday work with people with MS (Kazdin, 1999).

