## **Research design and methodology**

This is a mixed – method pilot design with the aim to explore feasibility and acceptability of the novel group psychological intervention MyMS-Ally. Quantitative and qualitative data will be collected in order to facilitate analysis of people with MS’ experience of the intervention as well as analysis of outcomes on quality of life, anxiety, depression and emotion regulation. The mixed-method design offers the framework for statistically significant conclusions to be made but also incorporate participants’ meaning – making accounts with an in-depth description of their experience of the intervention. The study adheres to an idiographic paradigm of exploring the impact of the intervention (Haynes et al., 2009; Molenaar, 2004) where each participant’s variations and changes over time are investigated through multiple points of collecting data. Following the patient – centred regime of the development of the intervention and the evaluation processes, the aim of the researchers is to identify tailored assessment processes that will eventually shed light on changes over time within each participant. Quantitative and qualitative methods are “compatible partners” in this research context (Onghema et al., 2019, p. 463) following a pragmatism epistemology combining action and reflection (Biesta 2010).

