## **Participants**

Recruitment and implementation of the intervention will take place in the Bristol and Avon Multiple Sclerosis Centre in Southmead Hospital, Bristol. A group of 5 - 6 participants will be recruited to take part in the MyMS-Ally group intervention. The group size reflects the minimum number of members of a group psychological intervention for meaningful interactions to be unfolded and the maximum number which allows enough time and space for each member to use the group effectively (Saracutu et al., 2018). The size of the sample also reflect the recommendations made in the PPI involvement focus group. Should more people with MS express interest in taking part, more than one groups will be offered. Eligible participants will be aged 18 years or above, diagnosed with multiple sclerosis more than two years ago, able to read, write and speak English and able to engage into eight weekly group psychological intervention sessions (2 months). The group intervention as well as data collection processes will take place online therefore access to the internet and to a device where they can use Microsoft Teams software on are required. People with MS with suspected and/or diagnosed comorbidity with Depression, Bipolar Disorder or Psychotic Disorders will not be able to participate in the study.

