### **Quantitative Data**

Descriptive statistics (means and standard deviations) will be calculated to provide insight into the participants' characteristics as well as indication of any potential changes in the mean scores between the different administration of the measures at four different points in time

(baseline, end of intervention, 1 month and 3 month follow up). Within subjects effects will also be calculated and reported. The final quantitative findings will be presented in a table reporting F, df, effect sizes, CI and p values.

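### The protocol aims for statistically significant results showing the intervention's impact, but an uncontrolled study with a committed size of 5-6 cannot attribute change and is unlikely to reach significance

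*Protocol*

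**What the plan says.** After setting out a feasibility and acceptability objective, the Purpose and design section adds that "the study aims to reach statistically significant results that will indicate the impact of the intervention". Research design and methodology returns to this: "The mixed-method design offers the framework for statistically significant conclusions to be made". Methods of Analysis, Quantitative Data, plans within-subject effects and states: "The final quantitative findings will be presented in a table reporting F, df, effect sizes, CI and p values".

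On size, the Participants section says: "A group of 5 - 6 participants will be recruited to take part in the MyMS-Ally group intervention". The reason given is group interaction and advice from the patient involvement group: "The group size reflects the minimum number of members of a group psychological intervention for meaningful interactions to be unfolded". It adds: "Should more people with MS express interest in taking part, more than one groups will be offered". The recruitment section and item 2 of the patient involvement statement repeat that further groups are possible. None of these places gives a number of groups, a target or a cap. Every participant receives the intervention.

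Three questionnaires (SWLS, HADS, ERQ) are completed at baseline, end of intervention, one month and three months. The Summary of the Study, Secondary objectives and Data collection sections describe these outcome data as preliminary.

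**The concern.** The two significance statements claim a property that the design lacks, and they conflict with the preliminary status given to the same data elsewhere.

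Two separate things are missing. The first is attribution. With no comparison group, change from baseline mixes any effect of the sessions with the natural course of MS, regression to the mean and non-specific attention. The second is sensitivity. A sample chosen so that a group can interact well was not chosen to detect anything.

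The study is meant to inform a later evaluation. If it is read against its stated aim, a non-significant table could be taken as lack of promise. A significant one could be taken as demonstrated impact, with an estimate too large to plan from.

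**Working it through.** **Plan's own figure.** There is none to reproduce. The protocol gives no significance level, power, effect size, SD or within-person correlation.

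**Inputs from the protocol.** n = 5 or 6 (Participants); four time points (Data collection); within-subject F tests with p values (Quantitative Data). The Summary of the Study reports that psychological interventions in MS "have been found to have moderate effects on quality of life", among other outcomes. That describes earlier interventions and gives no number.

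**Assumptions.** Two-sided 5% level; a change of 0.5 SD as one reading of moderate; within-person correlation ρ of 0.5 to 0.8.

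**Step 1, paired test of one follow-up against baseline.** Power comes from the noncentral t distribution with n − 1 degrees of freedom and noncentrality d√n, where d is in SDs of change.

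- n = 5: noncentrality 0.5 × √5 = 1.118, critical t = 2.776, power 14%.
- n = 6: noncentrality 0.5 × √6 = 1.225, critical t = 2.571, power 17%.

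Across a range of d, power for n = 5 / n = 6 is:

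- d = 0.3: 8% / 9%
- d = 0.8: 28% / 36%
- d = 1.0: 40% / 51%

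Reaching 80% power needs d of about 1.68 / 1.43. At d = 0.5 it needs 34 participants.

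**Step 2, F test over four time points.** Assume sphericity and the mean pattern 0, d, d, d, with d = 0.5 in SDs of the score. The sum of squared deviations is 0.75 × 0.5² = 0.1875. The noncentrality is n × 0.1875 / (1 − ρ), with 3 and 3(n − 1) degrees of freedom.

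| n | ρ | Noncentrality | Power |
|---|---|---|---|
| 5 | 0.5 | 1.875 | 14% |
| 5 | 0.7 | 3.125 | 22% |
| 5 | 0.8 | 4.688 | 31% |
| 6 | 0.5 | 2.250 | 17% |
| 6 | 0.7 | 3.750 | 27% |
| 6 | 0.8 | 5.625 | 39% |

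**Step 3, smallest observed paired change that reaches p < 0.05.** In SDs of change this is critical t / √n: 2.776 / √5 = 1.24 for n = 5 and 2.571 / √6 = 1.05 for n = 6. To convert to SDs of the score, multiply by √(2(1 − ρ)).

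- ρ = 0.5 (factor 1): 1.24 / 1.05
- ρ = 0.7 (factor 0.775): 0.96 / 0.81
- ρ = 0.8 (factor 0.632): 0.79 / 0.66

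All exceed 0.5. If the true change is about 0.5 score SD, any significant paired result at this size overstates it.

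**Step 4, sample sizes either side of 5-6.** Withdrawn participants' data are to be destroyed and left out of the analysis. One withdrawal from five leaves n = 4 and paired power of 11% at d = 0.5. Two full groups (n = 12) give 35% on the paired test and 36-76% on the F test for ρ from 0.5 to 0.8. Three (n = 18) give 52% and 54-93%.

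**Step 5, attribution.** This needs no arithmetic. Every participant is treated, so the analysis contains no estimate of what would have happened without the intervention. Larger n narrows the interval around the mean change but does not supply that comparison.

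**The case against.** The best defence is that the significance statements are marginal. The principal objective is feasibility and acceptability, explored mainly through interviews. The outcome data are called preliminary in several places. Descriptive statistics come first in the analysis section, effect sizes and confidence intervals are already planned, and no progression decision depends on a p value. All of that stands. It limits the damage and shows that the correction fits the rest of the plan. It does not make the two statements true.

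The second defence is the provision for more groups. It also stands in part: 5-6 is the committed size, not a ceiling, and with three groups and highly correlated scores the F test could be well powered. But no number is committed, and extra groups leave attribution unsolved.

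A reader might infer more than the documents support:

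- *That significance is impossible.* It is not. A very large change, or scores that correlate highly over time, could produce it.
- *That a significant change must be at least twice a moderate effect.* That compares SDs of change with SDs of the score. At ρ = 0.7 the threshold is 0.96 or 0.81 score SD, which is 1.9 or 1.6 times 0.5.
- *That the protocol itself expects a moderate effect of MyMS-Ally.* It uses the term for earlier interventions and contrasts MyMS-Ally with generic models.
- *That testing several scores without a multiplicity rule is a further error.* Such a rule may sit in an analysis plan that is not shown.
- *That the attainable p values of a signed-rank test matter here.* The protocol plans F tests.

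**Conclusion.** The point holds in this form: the protocol states an aim, and claims a design capability, that its uncontrolled design does not have. The attribution failure is independent of sample size and of every numerical assumption above. The power shortfall rests on the assumed 0.5 SD change, the two-sided 5% level, sphericity and the correlation range. At the committed size, power is 14-17% on the paired test at 0.5 SD of change and 14-39% on the F test over the whole correlation range. The overstatement argument applies to n of 5-6 and a true effect near 0.5 SD; it weakens as groups are added. The feasibility and acceptability objective is not affected.

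**What to change.** 1. Delete the significance aim in Purpose and design and the matching claim in Research design and methodology.
2. Describe the quantitative outcomes as preliminary throughout, in line with the Summary of the Study, Secondary objectives and Data collection sections. Add a sentence saying that the study is neither sized nor controlled to test efficacy or to attribute change to the intervention.
3. In the Quantitative Data table, give for each score the change from baseline to end of intervention, one month and three months with 95% confidence intervals, and show individual trajectories. State that no efficacy conclusion will rest on p values.
4. Keep the term impact for what participants report in interviews; perceived impact is a legitimate object of the qualitative work.

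The cost is wording only, with no added participants or data collection. The stated aim becomes less ambitious. The intervals will be wide: with five participants the half-width for a mean change is 1.24 SDs of change, and with six 1.05.

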### ***Potential issues***

A potential issue that may be raised in the study design is the demanding nature of the data collection methods. Participants will be asked to complete a battery of questionnaires (total 29 items) before, at the end of the intervention and at one and three – months follow - up. Participants will also be asked to engage in individual qualitative semi-structured interviews at baseline, at the end of the intervention and at 3 – months follow up. The potential burden of this level of data collection has been considered therefore short questionnaires have been selected to measure quality of life, depression, anxiety and emotion regulation. It is anticipated that it will take participants 10 – 15 minutes to complete the questionnaires. Online administration has been suggested in the study protocol. Moreover, the interviews have been planned to be conducted online through Microsoft Teams. The interviews will respect the participants' pace, needs and preferences; for example, have regular breaks during the interview. Moreover, following PPI involvement input, flexibility will be implemented in data collection stage so participants might prefer oral administration of questionnaires and/or they might prefer they have their carers attending the data collection sessions. It will be ensured that all potential participants will be fully informed of the study procedures prior to giving their consent.

The present research project has been discussed and reviewed by two experienced researchers in the field of Multiple Sclerosis and health research. [name], Associate Professor at the University of the West of England is the internal to the sponsor project supervisor. [name], Consultant Neurologist and Associate Professor in University of Bristol and North Bristol NHS Trust is overseeing the study procedures at the Bristol and Avon Multiple Sclerosis Centre where the recruitment and implementation of the intervention will take place. Moreover, the Research Network of the UK MS Society has been involved, consulting on the intervention implementation, the study design as well as dissemination strategies. Their input has affected the intervention implementation and study processes enhancing our aim to minimise risk and burden for participants and researchers.

### ***Recruitment and Inclusion/ Exclusion Criteria***

Participants will be recruited at the Bristol and Avon Multiple Sclerosis Centre, Southmead Hospital, North Bristol NHS Trust. The study will be presented to the multidisciplinary team of professionals who will then disseminate the research information, participant information sheet and consent form to people with Multiple Sclerosis (MS) that fit the inclusion and exclusion criteria. The potential participants who will be interested in participating or finding out more about the project will contact the Chief Investigator (CI) via phone, text or email (according to their preference) and they will have an initial discussion on what the intervention and study entail. This discussion will also serve as the initial screening where the CI will be able to explore how the potential participant fits the inclusion and exclusion criteria:

#### ***Inclusion Criteria***

- Participants must be able to read, write and speak English.
- Participants must be willing and able to give informed consent for participation in the study.
- Participants can be people who identify as men, women, non – binary, aged 18 and above.
- Participants must be diagnosed with Multiple Sclerosis and have received their first diagnosis more than two years ago.
- Participants must be cognitively and physically ready and willing to engage into eight weekly group psychological intervention sessions (discussed in screening meeting with potential participant).

- Participants should have access to the internet and to a device that will allow them to join the intervention and data collection processes through Microsoft Teams programme.

### *Exclusion Criteria*

The participants may not enter the study if ANY of the following apply:

- People with MS with suspected or diagnosed comorbidity with Depression, Bipolar Disorder or Psychotic Disorders (discussed at the screening stage with CI).
- People with MS that have received the MS diagnosis in the last two years prior to data collection point (avoid effects of newly diagnosed people with MS who would still be contemplating and making therapy decisions, there are specific needs that characterise this population).
- People with MS who are attending another psychotherapy or psychological intervention process at the time of application of MyMS-Ally group intervention.

All potential participants who will express their interest in the study will contact the CI and have an initial screening meeting and conversation. No one will be unfairly excluded from or included in the research. There will be no exceptions made regarding eligibility, i.e., that each participant must satisfy all the approved inclusion and exclusion criteria of the protocol. Potential participants will be aware of the intervention implementation design and the study procedures before they make an informed decision to participate in the study. The CI will be available to answer any further questions and provide clarifications after the initial/ screening discussion until the people with MS make their final decision. The potential participants will have two weeks to decide whether they are willing to participate after the initial meeting with the CI. The CI is a Chartered Counselling Psychologist with many years of clinical and academic experience and has been working with people with MS in a research context for the last five years. She feels confident she has the capacity to discuss and assess the impact the study will have on potential participants and also comprehends the ethical principles of delivering and evaluating a psychological intervention.

Those who will agree to participate will be asked to provide the CI with their demographics, email and telephone contact details in order to commence with the data collection process as well as to inform them of the start of the group intervention. Only the CI will have access to the participants' personal details. Five to six participants will be recruited and allocated to one group which will last two months (eight weekly sessions) following PPI involvement input. If more people with MS show interest in participating in the study, then more than one groups will be offered.

